### Secondary endpoints

Frequencies of early and late onset complications such as intra- or postoperative bleeding with subsequent need for blood transfusion, pancreatic fistula, postoperative pulmonary complications, wound infections and re-laparotomy; exocrine and endocrine pancreatic function as determined by levels of HbA1c and stool elastase.

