### The Beger procedure (reference treatment)

In 1972, H.G. Beger for the first time described the technique of duodenum preserving pancreatectomy in the treatment of patients with chronic pancreatitis (Fig. 1) [9,10]. The rationale of this intervention is the resection of the inflammatory mass in the pancreatic head without large loss of unaffected parenchyma and maintenance of the duodenal passage. Different studies have shown that this organ preserving technique is at least as effective as the more radical Kausch-Whipple procedure (pancreatico-duodenectomy) regarding pain control (effective pain diminishing in >80% within 5 years), but postoperative morbidity and the incidence of diabetes mellitus are lower [1,11-13].

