### The Berne procedure (selection of intervention)

Over the years, different variations of the duodenum preserving technique have been introduced. In 1985, Frey and Smith described a modification in which a longitudinal pancreatico-jejunostomy is combined with a local resection of the pancreatic head [14,15]. This technique combines the principle of duodenum preserving pancreatic head resection with the drainage of the main pancreatic duct. In 1998, similar to the Frey technique, Izbicki et al. combined the duodenum preserving resection of the pancreatic head with a V-shaped incision of the body of the pancreas in order to also reach II° and III° pancreatic side branches. The results obtained with this technique are very similar to the original Beger technique. Thirty patients were operated without mortality. After a median follow up of 30 months, 92% of the patients were pain free with preserved endocrine and exocrine function [16].

The main advantage of these variations of the original Beger procedure lies in the fact that the dissection of the pancreas from the portal vein can be avoided, which is regarded as the most hazardous part of the intervention [4]. Especially in case of portal vein thrombosis, the division of the pancreatic body from the portal vein, which is an essential step in the Beger (and also Kausch-Whipple) procedure, can be very demanding. Bleeding from the portal vein in this situation can be extremely difficult to control.

To combine the advantages of the original Beger procedure with the Frey technique, we developed an additional modification which consists in a duodenum preserving resection of the pancreatic head in analogy to the original Beger technique, with the difference that a small shape of pancreatic tissue remains on the anterior wall of the portal vein in a way that the hazardous division of vein and pancreatic body is avoided (Fig. 2) [17].

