## Study design

### Aim of the study

The objective of this trial is to compare two different surgical techniques for the treatment of chronic pancreatitis with regard to complication rates, length of operation, length of intensive care treatment, length of hospital stay, exocrine/endocrine pancreatic function and quality of life.

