## Randomisation and procedures for minimising bias

### Minimising systematic bias

In order to achieve comparable groups for known and unknown risk factors, randomization will be performed. The random allocation sequence was generated by a free available randomization software tool [18] by a trained independent study nurse not further involved in this trial. She also prepared the sealed and opaque envelopes for the randomisation procedure in the operation theatre. The sealed randomization list was stored in the investigator file. A sufficient number of patients will be recruited according to the sample size calculation in order to prevent random error. Patients will get randomised intra-operatively by an independent study nurse or anaesthesiologist once the surgeon decides that clinical equipoise is given, usually after the pancreas has been prepared and mobilised (Kocher's maneuver). All interventions will be done as described below. Patients in whom the randomised procedure cannot be performed due to technical or anatomical reasons will be analysed according the intention to treat principle.

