## Analysis

A flow chart according to the CONSORT statement is included [21]. The baseline characteristics of patients in both groups will be given in a table.

Comparisons will be made of the primary endpoints of both intervention groups for all patients included in the study on an intention to treat basis. Furthermore per protocol analysis will be performed as well as including only patients strictly treated according to the study protocol.

The outcome measures of the primary endpoint will be tested for significance with the Mann-Whitney Test (The test of H_0,1 _no *difference of duration of the surgical procedure *on the level of 5%). If the null hypothesis of no difference can be rejected the other components can be tested in a hierarchical way as follows (Fig 3):

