**Figure 3 F3:**
[figure not shown]
**Flow chart**. If the null hypothesis of no difference can be rejected the other components can be tested in a hierarchical way.

1. The test of H_0,2 _*Quality of life in both groups is not equivalent *is an equivalence test. Based on preliminary experiences with the EORTC QLQ-C30/PAN26 questionnaires in pancreatic cancer patients [20], we estimated baseline raw score values in the range of about 60 (SD 25) before therapy. When transformed into a percentage scale (with 100% indicating perfect health) this represents values of 45% (SD 18%). After surgery, quality of life can be estimated to improve up to value of 75% (SD 18%). We assume equivalence for the two resection techniques, if the two-sided 95% confidence intervals for difference in quality of life fall within the interval of +/-15%. The value of 15 as delta was chosen, because the overall effect of surgery is in the range of about 30 percentage points. Therefore, the minimal clinically relevant difference can be estimated by halving this effect of surgery. To show equivalence for a delta of 15 (SD 18) with alpha = 5% and beta = 20%, a sample size of 60 patients is required [22].

2. The test of H_0,3 _*Length of stay on the intensive care unit of both groups is not equivalent *is an equivalent test on the level of 5%. The zero-hypothesis is declined if the 90% confidence interval for the difference of mean values of ICU stay in hours for both groups is in between [-12/12 hours].

3. The test of H_0,4 _*Hospital stay on both groups is not equivalent *is an equivalent test on the level of 5%. The null-hypothesis is declined if the 90% confidence interval for the difference of mean hospital stay in days for both groups is in between [-2/2 days].

Once the null hypothesis cannot be rejected no further testing is applied. All secondary endpoints will be analyzed using descriptive and graphical methods.

Safety-related data will be analyzed with respect to frequency of:

• Severe bleeding intra- or postoperatively requiring blood transfusion

• Laparotomy

• Pancreatic fistula

• Pulmonary infection and wound infection are secondary endpoints, but are also defined as adverse events. Severe intraoperative bleeding with need for blood transfusion will even always be considered a serious adverse event.

Safety-related data will be analyzed with respect to frequency of:

• Serious adverse events and adverse events stratified according to the organ-systems

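### HbA1c level alone is a weak, treatment-sensitive measure of endocrine function; new-onset diabetes and glucose-lowering treatment should define the endpoint

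*Protocol article*

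**What the plan says.** The section Aim of the study names "exocrine/endocrine pancreatic function and quality of life" among the outcomes to be compared between the two techniques. The section Secondary endpoints then fixes how function is measured: "exocrine and endocrine pancreatic function as determined by levels of HbA1c and stool elastase". The article names no other endocrine measure.

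Diabetes is not among the exclusion criteria, so patients who already have it can be randomised. The background section on the reference procedure describes endocrine outcome differently. In comparing duodenum-preserving resection with the Kausch-Whipple procedure it reports that "postoperative morbidity and the incidence of diabetes mellitus are lower".

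On analysis, the text after Figure 3 says: "All secondary endpoints will be analyzed using descriptive and graphical methods". The endpoint has no test, margin or power. Follow-up interviews by blinded study nurses are planned at 6, 12 and 24 months (Minimising measurement bias).

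**The concern.** HbA1c shows how well blood glucose is controlled, which is not the same as how much islet function remains. Two problems follow.

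- **Masking by treatment.** A patient who loses endocrine function after surgery and starts glucose-lowering treatment can have an HbA1c close to that of a patient whose function is intact. Treatment starts after allocation and because of the outcome, so randomisation does not remove the effect. The better new diabetes is managed, the less the endpoint shows.
- **Noise from pre-existing diabetes.** A patient already diabetic brings a raised HbA1c that the operation did not cause. Such patients also cannot become new cases, which dilutes the contrast further.

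At stake is how a described result is read. With no formal test, similar HbA1c values in the two arms could be taken as similar endocrine function when one technique had led to more diabetes.

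**Working it through.** **The plan's own figures.** The article gives no figure for HbA1c or diabetes. Its sample size concerns operating time: a difference of 1 hour, SD 1 hour, two-sided alpha 0.05 (two-sided is assumed) and 90% power give 22 per group, as stated. Allowing for one third not receiving the intended procedure gives 44 / (2/3) = 66, against 65 stated. These figures do not bear on the point; they only supply about 65 / 2 ≈ 32 patients per arm.

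Everything below is illustration. The incidences, HbA1c values and shares with pre-existing diabetes are assumptions; none is in the documents.

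**Formula.** Let q be the share with pre-existing diabetes, equal in both arms. Let p1 and p2 be the incidences of new diabetes among the rest, h the mean HbA1c of new cases, and 5.5 the mean in non-diabetic patients. Then

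difference in mean HbA1c = (1 − q) × (p1 − p2) × (h − 5.5).

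**Illustration A:** p1 = 30%, p2 = 10%, q = 0; 32 per arm gives 9.6 against 3.2 new cases.

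- Untreated, h = 8.0: 0.20 × 2.5 = 0.50 points.
- All treated to h = 6.5: 0.20 × 1.0 = 0.20 points.
- All fully normalised, h = 5.5: 0.20 × 0 = 0.

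**Illustration B:** p1 = 25%, p2 = 10%; h = 8.5 untreated and 6.5 treated; pre-existing diabetes at mean 7.5. Assumed SDs are 0.4 (non-diabetic), 1.2 (pre-existing), 1.2 (untreated new) and 0.8 (treated new). The pooled SD comes from simulation.

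| Pre-existing | New cases treated | Difference | Pooled SD | Standardised |
|---|---|---|---|---|
| 0% | none | 0.15 × 3.0 = 0.45 | 1.28 | 0.35 |
| 0% | all | 0.15 × 1.0 = 0.15 | 0.62 | 0.24 |
| 20% | all | 0.80 × 0.15 × 1.0 = 0.12 | 1.06 | 0.11 |
| 40% | all | 0.60 × 0.15 × 1.0 = 0.09 | 1.27 | 0.07 |

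The difference in incidence is the same in every row, while the HbA1c contrast falls to between a third and a fifth of its untreated size (0.15 / 0.45 and 0.09 / 0.45).

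**Chance imbalance.** With q = 20% and 32 per arm, the SD of the difference in the share with pre-existing diabetes is √(2 × 0.20 × 0.80 / 32) = 0.10. At about 7.5 − 5.5 = 2.0 points per patient, this moves the difference in means by about 0.20 points (one SD), more than the 0.12-point signal in the same row. This is noise with expectation zero, not bias.

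**Would incidence do better?** It targets the right quantity, but a direct comparison of 25% with 10% at 32 per arm has only about 35% power. Restricting to patients not diabetic before surgery lowers the denominator to about 0.80 × 32 ≈ 26 or 0.60 × 32 ≈ 19 per arm.

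**The case against.** Several objections have force.

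- **The endpoint is secondary and only described.** This stands. It cannot affect the primary hierarchy, and the low power for incidence means that the replacement would be descriptive too. That limits the importance of the point, but does not make HbA1c level the better description.
- **Randomisation handles pre-existing diabetes.** The plan says: "In order to achieve comparable groups for known and unknown risk factors, randomization will be performed". It also promises that "The baseline characteristics of patients in both groups will be given in a table". This stands as regards bias: pre-existing diabetes mainly adds noise and dilution. It does not answer masking by treatment.
- **New diabetes may appear elsewhere.** The adverse event definition covers illness that arises or worsens during observation, and adverse events are analysed by organ system, severity and causality. An excess of diabetes could surface there. Diabetes is not named, however, and that route does not change how endocrine function is defined.
- **The background incidence statement concerns another comparison.** This also stands. It sets duodenum-preserving resection against the Kausch-Whipple procedure, whereas both arms here preserve the duodenum, and the advantage claimed for the new technique is avoiding dissection at the portal vein. The statement shows only that the article itself uses diabetes incidence as an endocrine outcome; this trial never had such an endpoint to replace.

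A reader might also infer that the trial set out to show preserved endocrine function. It did not: that wording, "92% of the patients were pain free with preserved endocrine and exocrine function", reports an earlier series, and the aim is only to compare function. Nor should a reader conclude that baseline samples are missing from the trial. A condensed article may leave sampling times to the full protocol.

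**Conclusion.** The point holds as a measurement weakness. HbA1c level is the only endocrine measure stated for a named objective, and treatment of diabetes arising after surgery pulls it toward no difference. Under the assumed values the mean difference falls from 0.50 to 0.20 points, or from 0.45 to 0.09–0.15, depending on the incidences and the share already diabetic. The direction of this effect follows from what HbA1c measures; its size rests wholly on assumptions.

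A reader might go further and say that the endocrine objective cannot be answered. The documents do not support that. HbA1c remains informative, the contrast shrinks without reversing, and it reaches zero only if treatment is assumed to normalise every new case. This is a low-cost improvement to a secondary, descriptive endpoint and has no bearing on the primary analysis.

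**What to change.** In Secondary endpoints, replace the HbA1c level as the definition of endocrine function by:

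- among patients not diabetic before surgery, new-onset diabetes by 12 and by 24 months, meaning HbA1c in the diabetic range (cut-off to be stated) or start of glucose-lowering treatment;
- among patients already diabetic, start or increase of glucose-lowering treatment over the same periods.

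Record treatment at the existing follow-up interviews. Keep HbA1c as a supporting measure, reported by treatment status and baseline diabetes. Stool elastase can stay as the exocrine measure.

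The cost is a question on glucose-lowering treatment at each of the 6-, 12- and 24-month contacts and a slightly longer case report form. The denominator for new-onset diabetes is smaller, and with about 32 patients per arm the result should be presented as counts and proportions, without a claim of equality or difference. If the full protocol already records diabetes and its treatment, only the endpoint definition has to change.

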## Adverse events and serious adverse events

The term *adverse event *(AE) covers any sign, symptom, syndrome, or illness that appears or worsens in a patient during the period of observation in the clinical trial and that may impair the well-being of the patient. The term also covers laboratory findings or results of other diagnostic procedures that are considered to be clinically relevant. A *serious adverse event (SAE) *is any adverse event that occurs at any time during the period of observation that results in death, is immediately life-threatening, requires or prolongs hospitalization, or results in persistent or significant disability or incapacity.

AEs will be reported to the principle investigator in regular intervals throughout the study.

SAEs which are meet one of definitions of the secondary endpoints are treated as SAEs regarding to documentation, but have not to be reported to the sponsor/principle investigator within 24 h.

## Analysis

A flow chart according to the CONSORT statement is included [21]. The baseline characteristics of patients in both groups will be given in a table.

Comparisons will be made of the primary endpoints of both intervention groups for all patients included in the study on an intention to treat basis. Furthermore per protocol analysis will be performed as well as including only patients strictly treated according to the study protocol.

The outcome measures of the primary endpoint will be tested for significance with the Mann-Whitney Test (The test of H_0,1 _no *difference of duration of the surgical procedure *on the level of 5%). If the null hypothesis of no difference can be rejected the other components can be tested in a hierarchical way as follows (Fig 3):

**Figure 3 F3:**
[figure not shown]
**Flow chart**. If the null hypothesis of no difference can be rejected the other components can be tested in a hierarchical way.

1. The test of H_0,2 _*Quality of life in both groups is not equivalent *is an equivalence test. Based on preliminary experiences with the EORTC QLQ-C30/PAN26 questionnaires in pancreatic cancer patients [20], we estimated baseline raw score values in the range of about 60 (SD 25) before therapy. When transformed into a percentage scale (with 100% indicating perfect health) this represents values of 45% (SD 18%). After surgery, quality of life can be estimated to improve up to value of 75% (SD 18%). We assume equivalence for the two resection techniques, if the two-sided 95% confidence intervals for difference in quality of life fall within the interval of +/-15%. The value of 15 as delta was chosen, because the overall effect of surgery is in the range of about 30 percentage points. Therefore, the minimal clinically relevant difference can be estimated by halving this effect of surgery. To show equivalence for a delta of 15 (SD 18) with alpha = 5% and beta = 20%, a sample size of 60 patients is required [22].

2. The test of H_0,3 _*Length of stay on the intensive care unit of both groups is not equivalent *is an equivalent test on the level of 5%. The zero-hypothesis is declined if the 90% confidence interval for the difference of mean values of ICU stay in hours for both groups is in between [-12/12 hours].

3. The test of H_0,4 _*Hospital stay on both groups is not equivalent *is an equivalent test on the level of 5%. The null-hypothesis is declined if the 90% confidence interval for the difference of mean hospital stay in days for both groups is in between [-2/2 days].

Once the null hypothesis cannot be rejected no further testing is applied. All secondary endpoints will be analyzed using descriptive and graphical methods.

Safety-related data will be analyzed with respect to frequency of:

• Severe bleeding intra- or postoperatively requiring blood transfusion

• Laparotomy

• Pancreatic fistula

• Pulmonary infection and wound infection are secondary endpoints, but are also defined as adverse events. Severe intraoperative bleeding with need for blood transfusion will even always be considered a serious adverse event.

Safety-related data will be analyzed with respect to frequency of:

• Serious adverse events and adverse events stratified according to the organ-systems

• Adverse events stratified by severity

• Adverse events stratified by causality

## Study organisation

All patients scheduled for duodenum preserving pancreatic head resection at the Department of Surgery, University of Heidelberg, will be referred to the Center for Clinical Studies in Surgery (KSC) [23] and screened by members of the KSC. Approximately 80 patients per year undergo a duodenum preserving pancreatic head resection for chronic pancreatitis at the Department of Surgery, University of Heidelberg. The estimated time frame to randomize 65 patients is approximately 18 months.

Data will be recorded in clinical reporting files. Double data entry will be done by two independent staff members and all analysis are performed with SPSS (SPSS, Chicago, IL) after plausibility controls and closure of the database.
